**Fig. 1 Fig1:**
[figure not shown]
Overall study design

### Who will take informed consent?

As the investigated study collective is per definition suffering from reduced consciousness, the patient’s legal representative will provide written informed consent. The informed consent of the patient will be sought retroactively as soon as possible. When the legal representative has not been named yet, a rapid application for a legal representative is initiated (in Germany called “Eilbetreuuung”).

### Additional consent provisions for collection and use of participant data and biological specimens

Not applicable.

### Interventions

#### Explanation for the choice of comparators

Not applicable.

### Intervention description

Intravenous amantadine at a dosage of 200 mg per day (100 mg each at 10:00 a.m. and 01:00 p.m.) will be applied for five days (120 h). If a patient presents as a non-responder (defined as an increase in GCS ≤ 2 points or a decrease in GCS) within the first 48 h after amantadine treatment initiation, the dosage will be increased after ECG control to 200 mg intravenously twice daily. Two independent clinical investigators score the patient separately to assess the primary endpoint. In case of disagreement, a third independent investigator will perform the GCS. Responding patients will remain on the 200 mg per day regime until day 5 (see Tables 2 and 3). This is in line with the recommendations for the dosage of amantadine in post-comatose patients with reduced vigilance (in traumatic brain lesions) (Summary of Product Characteristics (SmPC)) [42].

**Table 3 Tab3:** Dose schedule

	Morning 10.00 am	Noon 1.00 p.m.	Evening	Night	note
Day 1	100 mg	100 mg	0	0	
Day 2	100 mg	100 mg	0	0	
Day 3	100–200 mg	100–200 mg	0	0	Dose can be doubled in case of unresponsiveness to drug; minimum duration of treatment
	200 mg	200 mg	0	0	In case of non-responder
Day 4	100 mg	100 mg	0	0	
	200 mg	200 mg	0	0	In case of non-responder
Day 5	100 mg	100 mg	0	0	Maximum duration of treatment
	200 mg	200 mg	0	0	In case of non-responder Maximum duration of treatment

The trial medication will be administered intravenously in a clinical setting. The site investigator will keep an account of the trial medication and acknowledge the receipt of all shipments of the trial medication. The investigator will document the date of the dispensary, subject identification, batch/ serial numbers or other identification of trial medication.

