## Objectives

### Research hypothesis

Intravenous amantadine treatment over five days improves consciousness, defined as an increase in Glasgow Coma Scale (GCS) score of at least 3 points, in non-traumatic (neuro)intensive care unit patients.

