### Methods in analysis to handle protocol non-adherence and any statistical methods to handle missing data

No imputation of missing values is planned. The analysis population for the primary endpoint is defined as patients who show adherence to the study protocol to at least Visit 6 (GCS measurement after 5 days amantadine) and all patients who died until day 6 (failures). Dropouts before Visit 6 (e.g., anesthesia required) will be excluded from trial.

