### Biostatistician

[name].

**Composition of the data monitoring committee, its role and reporting structure**.

The data monitoring committee (DMC) is formed by the ZKS Tuebingen, Center for Clinical Studies. The DMC is independent from the principle investigator and sponsor. An interim-analysis is performed after 13 patients, undergoing amantadine treatment for at least 5 days. The study is terminated early if less than 4 successes are observed.

**Adverse event reporting and harms**.

**Safety assessment**.

Adverse events (AE), severe adverse events (SAE) and suspected unexpected serious adverse reactions (SUSAR) will be detected as exploratory endpoints within the study. A serious adverse event (SAE) means any untoward medical occurrence that at any dose:

results in death.is life-threatening.requires inpatient hospitalization or prolongation of existing hospitalization.results in persistent or significant disability/ incapacity.results in a congenital anomaly / birth defect.is medically significant (e.g., suspected transmission of an infectious agent via medicinal product).

Planned hospitalizations or prolongation of existing hospitalization as a result of the following causes need not to be reported as SAE:

drug application.test procedure required in the protocol.hospitalizations for diagnostic measures only.technical, practical, or social reasons, in absence of an adverse event.surgical intervention or other measures and the conditions leading to these measures are not AEs, if the condition leading to the measure was present prior to inclusion into the trial.stay at rehabilitation clinic.

Medical Dictionary of Regulatory Activities (MedDRA)-Coding will be used. All AE, SAE and SUSAR occurring after entry into the study and until day 14 after amantadine treatment (Visit 7) will be recorded. Within 24 h of occurrence, the adverse event has to be reported to the ZKS Tuebingen. The principle investigator or sponsor will determine relatedness of an event to study drug and decides potential termination of Amantadine treatment. The study will monitor for the following adverse events daily during patient examination: epileptic seizure, spasticity, ECG QTc > 480 ms, arrythmia, heart failure and hallucinations.

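### Treatment duration is stated in two incompatible ways (five days fixed; a day 3 minimum in Table 3), so it is unsettled how a patient whose course ends on day 3 or 4 is counted

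*Protocol article*

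**What the plan says.** **Fixed course.** The Research hypothesis reads "Intravenous amantadine treatment over five days improves consciousness". The Intervention description says the drug "will be applied for five days (120 h)" and adds: "Responding patients will remain on the 200 mg per day regime until day 5". The Abstract and the Trial design section also give five days, and the Abstract has the doubled dose running from day three to day five.

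**Range.** Table 3 (Dose schedule) carries the day 3 note "Dose can be doubled in case of unresponsiveness to drug; minimum duration of treatment". Its day 5 rows are marked as the maximum, for example "In case of non-responder Maximum duration of treatment".

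**Who is counted.**
- Statistical analysis: the primary population is every patient with a day 6 GCS, plus deaths up to day 6 as failures. There is no condition on treatment duration. Patients who cannot be evaluated are replaced.
- Methods in analysis to handle protocol non-adherence: the population is patients adherent to at least Visit 6, described as "GCS measurement after 5 days amantadine", plus deaths. Dropouts before Visit 6 are excluded.
- Paragraph on the data monitoring committee (printed under the Biostatistician heading): the interim analysis is taken after 13 patients "undergoing amantadine treatment for at least 5 days". The Sample size calculation and Interim analyses sections say only that it follows 13 patients.

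**The concern.** A minimum on day 3 and a maximum on day 5 describe a range, whereas the text describes a single course. The stopping rules for allergy and toxicity are triggered by events at any time, so they do not explain a planned minimum. Table 4 changes the dose for renal function, not the duration.

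The difference matters because it reaches the one confirmatory test. For a patient whose course ends on day 3 or 4, the documents support two answers: counted by the Visit 6 GCS, or non-adherent and replaced. The investigators see the patient's course and treatment is open-label, so the choice could follow the observed response. It would affect the denominator at both the interim look and the final analysis.

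**Working it through.** **1. The statements side by side, for a patient whose last dose is on day 3 and who has a Visit 6 GCS**

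| Place | Treatment of this patient |
|---|---|
| Table 3, day 3 note | Minimum duration met |
| Intervention description, text | Five-day course not completed |
| Statistical analysis | In the primary population |
| Protocol non-adherence section | In or out, depending on whether five days of drug is a condition or only a label for Visit 6 |
| Data monitoring committee paragraph | Not among the 13 interim patients if read literally |

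**2. What the Visit 6 GCS would measure.** Take the first dose at 10:00 on day 1 as hour 0. Table 3 then puts the last dose at 51 h (day 3, 13:00) or 99 h (day 5, 13:00). Visit 6 is at 120 ± 4 h, that is 116 to 124 h. The gap from last dose to assessment is 116 − 51 = 65 to 124 − 51 = 73 h after a 3-day course, against 17 to 25 h after a 5-day course. Cumulative dose, like for like:
- undoubled: 3 × 200 = 600 mg against 5 × 200 = 1000 mg (1.7-fold);
- doubled from day 3: 2 × 200 + 400 = 800 mg against 2 × 200 + 3 × 400 = 1600 mg (2-fold).

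**3. The plan's own design reproduces.** Inputs from the Sample size calculation: p0 = 0.20, p1 = 0.40, stop if fewer than 4 of 13 succeed, trial successful if at least 13 of 43 succeed.

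P(success | p) = Σ (x = 4 to 13) C(13, x) pˣ (1 − p)¹³⁻ˣ × P[Bin(30, p) ≥ 13 − x]

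This gives 0.0496 at p = 0.20 and 0.800 at p = 0.40. A grid search for the smallest expected sample size under p0 returns the same design (3/13, 12/43).

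**4. Effect of excluding and replacing these patients.** Let s be the share of patients excluded because their course ended early, and q their success rate. Neither is in the documents; both are assumptions. With an overall rate of 0.20, the rate among those counted is

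p_c = (0.20 − s·q) / (1 − s)

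For example, s = 0.10 and q = 0 gives 0.20/0.90 = 0.222; s = 0.10 and q = 0.40 gives 0.16/0.90 = 0.178. Putting p_c into the formula in step 3, with exclusion at both stages (p_c, then type I error):

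| s | q = 0 | q = 0.20 | q = 0.40 |
|---|---|---|---|
| 5% | 21.1%, 6.9% | 20.0%, 5.0% | 18.9%, 3.4% |
| 10% | 22.2%, 9.7% | 20.0%, 5.0% | 17.8%, 2.1% |
| 15% | 23.5%, 13.5% | 20.0%, 5.0% | 16.5%, 1.2% |
| 20% | 25.0%, 18.6% | 20.0%, 5.0% | 15.0%, 0.6% |

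Excluding patients who did not improve raises the error; excluding patients who had already woken lowers it. If they are counted by their Visit 6 GCS, this source of bias is absent.

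**The case against.** The best defence is that the protocol has a five-day course and one stray table note. Table 3 itself prescribes doses on days 4 and 5 for responders and non-responders alike, with no optional or zero row. The text keeps responders on drug to day 5 and raises the dose for non-responders. Early ends for allergy, toxicity or the subject's objection have their own rules. The Statistical analysis section already counts anyone with a day 6 GCS, and the mention of five days in the non-adherence section can be read as a description of Visit 6, in line with the visit labels in Table 2.

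Most of this stands, and it limits the point. A reader might infer four stronger things that the documents do not support:
- **Three different durations.** At least five days, with a maximum on day 5, means five days. The interim wording agrees with the five-day text and conflicts only with the day 3 note.
- **Certain exclusion of a patient stopped on day 3.** That requires reading the non-adherence section as a duration condition; the Statistical analysis section says otherwise.
- **An inflated type I error.** The direction depends on who stops, and no stopping rate is given.
- **A 2.7-fold dose range (1600/600 mg) caused by the duration conflict.** That comparison mixes in the planned doubling. Duration alone gives 1.7-fold or 2-fold.

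The defence does not explain why the table names a minimum on day 3, and it does not remove the second reading of who is evaluable.

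**Conclusion.** The contradiction is real and lies in operative text: a fixed five-day course against a day 3 minimum in the dose table. Its statistical consequence is conditional. It arises only if some courses end on day 3 or 4, and only if those patients are then treated as non-adherent and replaced. Under the assumed shares of 5% to 20%, type I error could lie anywhere from 0.6% to 18.6%, depending on how the excluded patients would have scored; it stays at 5.0% if they respond like the rest. These figures illustrate sensitivity and do not estimate what will happen. The sample size and the Simon boundaries are correct as stated. This is a wording fault that should be corrected because it leaves a discretionary route to exclusion in an open-label, single-arm test; it is not a fault in the design calculation.

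**What to change.** 1. Reconcile the minimum and maximum notes in Table 3 with the text of the Intervention description, the non-adherence section and the data monitoring committee paragraph, so that one duration rule stands throughout. Which duration applies is for the sponsor to decide.
2. Align the non-adherence section and the data monitoring committee paragraph with the Statistical analysis section: a patient whose course ends early but who has a Visit 6 GCS is counted by that GCS at both the interim and the final analysis, and is not replaced.
3. Record the number of doses given, so that exposure can be described.

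The cost is a minor amendment of wording, with no extra patients, visits or procedures and no change to the Simon boundaries.

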### Criteria for discontinuing or modifying allocated interventions 

#### Renal function impairment

As the renal clearance of amantadine is significantly lower in adult patients with moderate or severe renal impairment compared with healthy adults and the renal pathway is a major elimination pathway, impairment in renal function can result in significant accumulation in the plasma. In case of renal insufficiency, the dosage will be modified according to the dose adjustment table (see Table 4).

**Table 4 Tab4:** Dose modification in case of renal insufficiency

Glomerular filtration rate (GFR) in ml/min	Dosage modification in mg	Administration interval
80 − 60	no dosage modification	
60 − 50	no dosage modification	
50 − 30	100 mg	1-1-0 No increase in non-responders
30 − 20	100 mg	1-0-0 no increase in non-responders
20 − 10	100 mg	1-0-0 no increase in non-responders
< 10 or hemodialysis	excluded from trial	

#### Allergic reactions

Amantadine might provide unknown allergic potential. If this is suspected withdraw the medication from the patient. This should be reported as an adverse event.

#### Toxicities

If treatment-related toxicities occur during the study, especially epileptic seizure, spasticity, ECG QTc > 480 ms, or any other suspicious ECG changes or cardial events (e.g., arrythmia, myocarditis, heart failure), drug administration will be terminated immediately. This should be reported as an adverse event.

If hallucinations occur, the dosage will be decreased to 50%. If successful, the administration will be continued with the reduced dosage, otherwise, it will be abandoned entirely. This should be reported as an adverse event.

#### Overdosage

The acute amantadine intoxication state is characterized by nausea, vomiting, hyperexcitability, tremor, ataxia, blurred vision, lethargy, depression, dysarthria and cerebral seizures; malignant cardiac arrhythmia has been reported in one case.

Acute toxic psychosis in the form of confusional/ delirium with visual hallucinations up to coma, as well as myoclonus, has been observed with concomitant administration of amantadine with other antiparkinsonian drugs.

No specific drug therapy or antidote is known in case of intoxication. In case of oral intake, vomiting should be induced or gastric lavage should be performed. In the case of vitally threatening intoxication, intensive monitoring measures are also required. Therapeutic options include fluid intake, acidification of the urine for faster excretion of the substance, sedation if necessary, anti-seizure medication, and antiarrhythmic drugs (lidocaine i.v.). To treat neurotoxic symptoms (as described above), intravenous administration of 1–2 mg physostigmine every 2 h can be tried in adults up to a maximum dose of 2 mg. Due to the low dialysability of amantadine (approx. 5%), hemodialysis is not advisable. It is recommended to monitor patients particularly with regard to a possible QT prolongation and factors favoring the occurrence of torsade de pointes, e.g., electrolyte disturbances (especially hypokalemia and hypomagnesaemia) or bradycardia.

### Strategies to improve adherence to interventions

Not applicable. ANNES Trial is performed in intensive care units, where research physicians control the medication every day.

### Relevant concomitant care permitted or prohibited during the trial

The administration of other medication prolonging QT time (e.g., Class IA and III antiarrhythmic drugs, antipsychotics, macrolide antibiotics) is not permitted during treatment with amantadine. If this is necessary due to a medical condition, QT time must be closely monitored. Moreover, administration of medication reducing consciousness (e.g., propofol, ketamine) should be avoid.

### Provisions for post-trial care

Patients that are enrolled in the ANNES study are insured through HDI Global SE in case of negligent harm or death during amantadine treatment. The maximum payment by the insurer for a single patient is limited to 500.000 Euro.

### Participant timeline

The individual study duration will be three months comprising of eight study visits in total (one screening visit, five visits during the treatment period and two follow-up visits, one two weeks after last medication intake and one at follow-up after three months).

### Statistical planning

#### Sample size calculation

The sample size is calculated using the two-stage optimum design of Simon for Phase II trials (see link below or nQuery Sample Size Software). Using this design, we proceed as follows: First we define a favorable true success rate of 40% successes which should lead with 80% power to a successful study. If this rate is 20% or smaller, the study should be with probability of at most 5% (type 1 error, one-sided) successful. We include 43 evaluable patients in the trial. After 13 patients, an interim analysis for futility is performed. The study is terminated early if less than 4 successes are observed. If four or more successes are observed, the study continues with 30 additional patients to recruit a total of 43 patients. According two-stage optimum design the final cut-off are 12 patients. Therefore, the study is successful if at least 13 of 43 patients show an increase of GCS score of at least 3 points (see supplemental Figs. 1 and 2):

#### Statistical analysis

The study is successful if a total of 13 of 43 patients show success (improvement of at least 3 points on the GCS). Using the two-stage optimum design of Simon for Phase II trials, non-evaluable patients have to be replaced. However, if the necessary number of 13 successes is achieved with less than 43 patients, there will be no early stopping for success. Calculations have been done with a Simon design calculator presented by the NIH on the internet: http://linus.nci.nih.gov/cgi-bin/simonr/cgi_main.

The primary endpoint *improvement of the GCS score from screening up to day 5 of at least 3 points* is analyzed according to the Simon design as described above. The primary analysis population is the per protocol population. This population includes all patients with GCS measurement at day 6 and all patients who died until day 6 (failures). No planned subgroup analyses will be performed. The secondary endpoints (mRS, NIHSS, GOS-E, CRS-R, MoCA after 90 days, RASS and ICDSC) will be analyzed by mixed models with time (categorially coded) as only factor including all measurements up to 3 months follow up. In case of severe violation of normal distribution assumption data will be analyzed by nonparametric tests (Friedmann with including pairwise comparisons using Nemenyis test). No imputation of missing values is planned. P-values will be computed, significances are only “local” in the sense that they are not corrected for multiple testing. The only confirmatory analysis is the one for the primary endpoint.

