### Secondary objectives and endpoints

Secondary objectives are improvement of vigilance/awareness measured via alternative scales using the following: Richmond Agitation-Sedation Scale (RASS), Full Outline of UnResponsiveness (FOUR) Score Coma Scale, Glasgow Outcome Scale – Extended (GOS-E) and Coma Recovery Scale revised (CRSR). Further secondary outcome variables include functional outcome using National Institute of Health Stroke Scale (NIHSS) regarding potential stroke severity and modified ranking score (mRS) in follow-up after discontinuation of medication and after three months. The incidence of complications regarding delirium will be assessed using the Intensive Care Delirium Screening Checklist (ICDSC). The Montreal Cognitive Assessment (MoCA) will assess the neuropsychological outcome. Regarding validity of these measures for determining outcome, please see the paragraph below.

Any adverse event (AE) (any untoward medical occurrence including an abnormal laboratory finding, regardless of its causal relation to the study treatment) will be recorded during the whole study period.

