#### Delirium

A clinician can easily and quickly apply the ICDSC. The ICDSC can easily and quickly be applied by a clinician or a nurse in the critical care setting to screen all patients for a delirium (even when communication is compromised in case of aphasia) [35].

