### Patient population and eligibility criteria

Patients are screened for eligibility according to the inclusion and exclusion criteria (for detailed description, see Table 1). All relevant medical and non-medical conditions should be considered when deciding whether the study is suitable for a particular patient. A screening sheet is used to assess the persisting, not otherwise explained coma to ensure that relevant differential diagnoses have been excluded. To be eligible, patients must be aged 18 years or older with prolonged (≥ 72 h) and persisting coma not otherwise explained with a Glasgow Coma Scale (GCS) < 8. The exclusion criteria for this study were chosen according to the official contraindications for amantadine [42]. In addition, patients with unresponsive wakefulness (UWS) or minimally conscious state (MCS) are excluded. As the investigated study collective is per definition suffering from reduced consciousness, the patient’s legal representative will provide written informed consent. No gender ratio has been stipulated in this trial as one previous clinical study did not indicate any gender difference in the effect of the trial treatment in terms of efficacy and safety [43].

**Table 1 Tab1:** Inclusion and exclusion criteria

Inclusion criteria	Details
Coma with reduced consciousness with GCS < 8	Lasting at least 72 h, not otherwise explained
Age ≥ 18 years	at the time of signing the informed consent.
Inconspicuous EEG and ECG	-
In woman of child bearing potential: pregnancy excluded	By measurement of human chorionic gonadotropin (hCG) in serum before start of study medication
Informed consent	As subjects per definition suffer from reduced consciousness and therefore are not in a position to provide informed consent themselves, prior to any study related procedures, the patient’s legal representative has to give written informed consent. The informed consent of the patient will be sought retroactively as soon as possible.
Exclusion criteria	
Reduced consciousness, otherwise sufficiently explained	Such as reduced consciousness due to status epilepticus, hyperglycemia, electrolyte imbalance, hyperkaliemia, akinetic crisis in Parkinson’s Disease or Delirium (Intensive Care Delirium Screening Checklist (ICDSC) > 4 or > 5 in aphasic patients)
Age < 18 years	**-**
Participation in other interventional study	Participation in an observational trial is acceptable
History of epileptic seizures/status epilepticus	-

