### Methods for additional analyses (e.g., subgroup analyses)

No planned subgroup analyses will be performed.

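### Delirium is announced as an incidence, but the only planned ICDSC analysis compares scores between visits and cannot give an incidence

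*Protocol article*

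**What the plan says.** Under Secondary objectives and endpoints, the delirium outcome is an incidence: "The incidence of complications regarding delirium will be assessed using the Intensive Care Delirium Screening Checklist (ICDSC").

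Under Statistical analysis, ICDSC appears once, at the end of the list of secondary endpoints: "RASS and ICDSC) will be analyzed by mixed models with time (categorially coded) as only factor", using every measurement through the three-month visit. The fallback follows: "In case of severe violation of normal distribution assumption data will be analyzed by nonparametric tests", namely Friedman's test with Nemenyi pairwise comparisons. The same section makes the primary endpoint the only confirmatory analysis.

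The only ICDSC threshold for delirium is in Table 1, among the exclusion criteria: "Intensive Care Delirium Screening Checklist (ICDSC) > 4 or > 5 in aphasic patients". The Delirium section says that the checklist serves "to screen all patients for a delirium (even when communication is compromised in case of aphasia"), so aphasic patients are expected.

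Table 2 schedules ICDSC at every visit from 1 to 8. It also has eligibility rechecked at Visit 1, the visit at which the baseline ICDSC is scored.

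**The concern.** An incidence is a proportion of patients who meet a case definition. The plan names an instrument for it and then fixes an analysis of that instrument that contains no case definition. It has not simply left the analysis open: the analysis it specifies answers a different question, namely whether the average or typical score differs between visits.

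The study is single-arm and open-label, and the Discussion sees its data as input to a later placebo-controlled trial. A delirium rate with its uncertainty would be useful for that. The Discussion also calls it crucial to separate reduced consciousness due to the primary disease from superimposed delirium, and names the ICDSC for this purpose. A table of visit means or a Friedman p-value gives no such rate.

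**Working it through.** The protocol states no figure for the delirium endpoint, so there is none to reproduce. The sample size of 43 is taken from the Simon design, which does reproduce: stop if fewer than 4 of 13, succeed with at least 13 of 43, one-sided type 1 error 0.0496 at 20%, power 0.8002 at 40%.

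**1. What the planned analysis estimates.** With categorical time as the only factor, the mixed model estimates one mean per visit across patients. Friedman's test compares within-patient ranks across visits. Neither output is a count of patients above a threshold.

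**2. Do visit means determine the incidence?** Inputs: 43 patients, the seven post-baseline visits (2 to 8), cut-off > 4. Three data sets were constructed so that the scores at each visit sum to 43 × 3 = 129, a mean of exactly 3.0:

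| Data set | Scores at each visit | Patients ever above 4 |
|---|---|---|
| A | all 43 patients score 3 | 0 (0%) |
| B | the same 6 patients score 7; the other 37 share 129 − 42 = 87 points, each scoring 2 or 3 | 6 (14%) |
| C | as B, but a different 6 patients score 7 at each visit | 42 (98%) |

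The visit means are identical in all three, while the incidence runs from 0% to 98%.

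**3. The reverse direction.** Suppose that 13 of 43 patients become delirious, scoring 6 instead of 1 (an illustration, not an expected rate). If each has one such visit, spread evenly over Visits 2 to 6, each visit mean rises by (13/5) × 5/43 = 0.30 points. If all 13 stay delirious over Visits 2 to 6, each mean rises by 13 × 5/43 = 1.51 points. The incidence is 13/43 = 30% in both cases.

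**4. The aphasia-specific threshold.** A score of 5 is above the eligibility cut-off in a non-aphasic patient and not in an aphasic one. If a single > 4 rule were used, the number misclassified would be 43 × (share aphasic) × (share whose highest score is exactly 5). With assumed shares of 10% to 50% and 5% to 15%, this runs from 43 × 0.10 × 0.05 = 0.2 to 43 × 0.50 × 0.15 = 3.2 patients.

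**5. The capped baseline.** Patients above the cut-off are excluded, so the Visit 1 score cannot exceed 4 (5 if aphasic), while later scores are not capped. The documents give no ICDSC distribution, so the following inputs are assumptions: score range 0 to 8, underlying mean 3 or 4, SD 2, correlation between visits 0.5 to 0.9, no true change, entry only if the first score is at most 4. In simulation the later mean exceeded the baseline mean by 0.09 to 0.67 points, and 7% to 27% of patients were above 4 at a given later visit.

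**6. What an incidence would look like.** For x of n patients, the exact (Clopper-Pearson) 95% limits are the 2.5% quantile of Beta(x, n − x + 1) and the 97.5% quantile of Beta(x + 1, n − x). With n = 43: 0/43 = 0% (0% to 8.2%); 4/43 = 9.3% (2.6% to 22.1%); 13/43 = 30.2% (17.2% to 46.1%).

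**The case against.** The strongest reply is that the gap is small. ICDSC is recorded at every visit, so a count above a cut-off needs no new data; nothing in the analysis section forbids it; and such derivations are often left to an analysis plan, which is not shown here. Adverse events are also recorded, so delirium could be captured that way, and the endpoint is not confirmatory. All of this lowers the weight of the point. It does not remove the mismatch: the protocol assigns the incidence to the ICDSC and then names an analysis of the ICDSC that cannot supply it.

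Three stronger readings are tempting, and the documents do not support them.

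- A reader might infer that the analysis disregards a stated endpoint definition. It does not: the > 4 / > 5 rule is given only for eligibility. The accurate statement is that it is not carried into the outcome.
- A reader might infer that the capped baseline biases the delirium endpoint. It affects only contrasts of scores with Visit 1, not those among later visits, and a delirium-free entry population suits an incidence of new delirium.
- A reader might take the Overdosage section to list delirium as part of amantadine intoxication itself. That section ties confusional or delirious psychosis to co-administration with other antiparkinsonian drugs, so it does not make delirium a known effect of the study drug alone.

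A simple any-visit proportion also has limits. It rises with the number of scorable visits, and fluctuation alone can push patients over the threshold, as step 5 shows. It must be reported as description.

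**Conclusion.** The point holds as a mismatch between a stated secondary outcome and its only stated analysis. That visit means do not determine the incidence follows from the constructed data sets and needs no assumption about the true delirium rate. The possible upward drift from Visit 1 is real in direction wherever scores vary between visits, but its size is unknown; 0.09 to 0.67 points depends wholly on assumed inputs. The effect of the aphasia-specific threshold, up to about 3 of 43 patients, is likewise assumed. The primary analysis and its decision rule are not touched. The change should be made because it is cheap and the stated outcome is otherwise not delivered.

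**What to change.** In the Statistical analysis section, add a delirium analysis along these lines:

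- **Case and estimate:** the number and proportion of treated patients with ICDSC above the protocol's own cut-off (> 4; > 5 if aphasic) at any post-baseline visit, with an exact 95% confidence interval.
- **Denominator:** treated patients with at least one scorable post-baseline ICDSC.
- **By visit:** the number scorable and the number above the cut-off at each visit, with Visits 2 to 7 and Visit 8 shown separately. Table 2 ends adverse event documentation at Visit 7, and Visit 8 comes at three months.
- **Score model:** keep the ICDSC mixed model (or its rank-based fallback) as descriptive only, and note that contrasts with Visit 1 start from a score capped by eligibility.
- **Interpretation:** state that the any-visit proportion is descriptive, depends on the number of scorable visits, and in a single-arm trial does not attribute delirium to the drug.

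The cost is one paragraph and a short derivation from assessments already scheduled. Aphasia status is already needed to apply the eligibility rule. The downside is a wide interval at this sample size, as in step 6 of the working.
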